**Methods:**

This paper describes the protocol for a cluster randomized controlled trial. We will randomly assign 18 primary-care practices per participating region of Spain (Catalonia, Madrid and Canary Islands) to a virtual community of practice or to usual training. The primary-care practice will be the randomization unit and the primary healthcare professional will be the unit of analysis. We will need a sample of 270 primary healthcare professionals (general practitioners and nurses) and 1382 patients. We will perform randomization after professionals and patients are selected. We will ask the intervention group to participate for 12 months in a virtual community of practice based on a web 2.0 platform. We will measure the primary outcome using the Patient-Provider Orientation Scale questionnaire administered at baseline and after 12 months. Secondary outcomes will be the sociodemographic characteristics of health professionals, sociodemographic and clinical characteristics of patients, the Patient Activation Measure questionnaire for patient activation and outcomes regarding use of the virtual community of practice. We will calculate a linear mixed-effects regression to estimate the effect of participating in the virtual community of practice.

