### Randomization

We will perform allocation by clusters — with the PCP as the randomization unit — to minimize possible contamination effects among professionals. An investigator blinded to PCP identity and to baseline PPOS and PAM results will centrally perform randomization after professionals and patients are selected. This investigator will randomly assign 54 PCPs (nine pairs for each of the three regions, each randomly assigned a code) to either the e-MPODERA virtual COP group or the control group (27 PCPs per group) using Epidat 4.1 software (balanced group option). The unit of analysis will be the primary healthcare professional. To reach the necessary sample size, each professional will be required to recruit at least six consecutive patients. Figure 2 depicts a flowchart of the randomization procedure.

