### Data collection, management and analyses

We will collect a mixture of professional and patient-reported data, using validated questionnaires for the primary and most of the secondary outcome measures. We will require each recruiting site to keep accurate and verifiable source notes regarding each participant’s inclusion and continued participation in the study. We will collect, transfer and store data in accordance with Good Clinical Practice (GCP) guidelines and data protection requirements. The e-MPODERA standard operating procedures (SOPs) and study data management plan will define the exact procedures for collecting, transferring, storing and quality-controlling study data.

We will perform descriptive and exploratory analyses, including cluster analyses according to participant baseline characteristics, using means and standard deviations for continuous variables and proportions for categorical variables. We will compare the two groups in terms of PPOS scores, PAM scores and descriptive variables. We will perform inferential analysis using the Mann-Whitney U test — with a 95% confidence interval — to compare across-group results in the PPOS and PAM tests in terms of score at 12 months from baseline.

We will perform a multilevel analysis of models for the main outcome (the PPOS test), where the response variable will be the difference between initial and final scores in the questionnaire administered to participating professionals and the explanatory variable will be the dichotomous intervention variable (1 = COP/0 = control). This model considers covariates such as age, sex and professional profile and also takes into account the random effect associated with the COP. We will use the propensity score to control for possible selection bias and enhance the accuracy of the model.

We will perform intention-to-treat analyses using the statistical software (http://www.R-project.org/) and PASW Statistics 18. We will use the last observation carried forward to impute missing data and will report analyses with and without imputation. We will inform participants that they can leave the study at any time. We will report missing data, if applicable, by categorizing the participants as follows: mistakenly randomized, did not receive the intervention, withdrew consent, crossed over, dropped out, did not adhere, lost contact or other reasons not specified [33].

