## Abbreviations

COP: Community of practice
e-MPODERA: Effectiveness of a Virtual Intervention to Improve Healthcare Professional Attitudes to Patient Empowerment
GCP: Good Clinical Practice
GP: General practitioner
PAM: Patient Activation Measure
PCP: Primary-care practice
PI: Principal investigator
PPOS: Patient-Practitioner Orientation Scale
SOP: Standard operating procedure

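### The primary PPOS model attaches its random effect to the COP, which is the intervention, and not to the randomised practice (PCP); probably a slip, but wrong as written

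*Protocol article*

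**What the plan says.** The Data collection, management and analyses section specifies a multilevel model for the change in PPOS score. For its fixed part, "the explanatory variable will be the dichotomous intervention variable (1 = COP/0 = control"). On adjustment, "This model considers covariates such as age, sex and professional profile". The same sentence then gives the random part: the model "also takes into account the random effect associated with the COP".

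The Abbreviations section separates the two terms: "COP: Community of practice" and "PCP: Primary-care practice".

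The design is stated in the abstract: "The primary-care practice will be the randomization unit and the primary healthcare professional will be the unit of analysis". The Randomization section agrees, describing allocation "with the PCP as the randomization unit" and assigning 54 practices "to either the e-MPODERA virtual COP group or the control group (27 PCPs per group"). The Sample size section applies a design effect of 1.12, from an ICC of 0.03 and an average of five professionals per cluster.

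The abstract announces a linear mixed-effects regression without naming a grouping factor. Additional measures lists the PCP among the data recorded for each professional. Nowhere does the article put the PCP into the model, as a random or a fixed effect.

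**The concern.** The same label appears twice in one model, first as the fixed treatment contrast and then as the source of the random effect. The Intervention section describes a single virtual COP, and control professionals belong to none. A grouping factor based on the COP therefore has two levels, and these are the two arms. It cannot carry the correlation between colleagues in one practice, which is what the design effect was meant to cover.

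The other inferential method named for PPOS, a Mann-Whitney U test, is described without any cluster term. If the multilevel sentence is followed to the letter, no inferential analysis in the article reflects the unit that was randomised. What is at stake is the standard error, confidence interval and p-value of the primary effect.

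**Working it through.** **Inputs (Sample size and Randomization sections).** Difference 0.2, SD 0.5, alpha 0.05 (two-sided reproduces the stated figure), power 80%, ICC 0.03, five professionals per cluster, 20% loss, 27 practices per arm.

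**1. The plan's own figure.**
- Normal approximation: 2 × (1.96 + 0.84)² × 0.5² / 0.2² ≈ 98.1, so 99 per group. The t-based solution is 99.08, rounded up to the stated 100.
- Design effect: 1 + (5 − 1) × 0.03 = 1.12, giving 100 × 1.12 = 112 per group.
- Loss: 112 × 1.2 = 134.4, rounded up to 135 per group, 270 in total.

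The stated 270 is reproduced, and it contains the allowance for clustering by practice.

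**2. Can a COP random effect be identified?** Take the fixed-effect matrix X (intercept and arm, 135 professionals per arm) and add the indicator columns Z of a COP/control random effect. The rank of X is 2 and the rank of [X Z] is also 2. The random effect lies wholly within the space of the fixed treatment term. Its variance cannot be separated from the treatment effect, and it absorbs no between-practice variation.

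**3. Consequence if the model reduces to ordinary regression.** With design effect DE, the naive standard error is too small by 1 − 1/√DE, and the true two-sided type I error is 2 × [1 − Φ(1.96/√DE)].

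| ICC | DE (5 per practice) | SE too small by | Type I error |
|---|---|---|---|
| 0.01 (assumed) | 1.04 | 1.9% | 5.5% |
| 0.03 (planned) | 1.12 | 5.5% | 6.4% |
| 0.05 (assumed) | 1.20 | 8.7% | 7.4% |
| 0.10 (assumed) | 1.40 | 15.5% | 9.8% |

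At the planned ICC, coverage of a nominal 95% interval is about 93.6%.

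**4. Simulation check.** In 20,000 simulated null trials with 27 practices of five per arm and ICC 0.03, the analysis ignoring practice rejected in 6.5%. An analysis of practice means rejected in 5.1%.

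**5. Sensitivity to cluster size.**
- With 20% loss, four completers per practice remain: DE = 1 + 3 × 0.03 = 1.09, type I error about 6.0%.
- Unequal practices work the other way. For an assumed coefficient of variation of 0.6, DE = 1 + [(1 + 0.36) × 5 − 1] × 0.03 = 1.174, type I error about 7.0%.

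**The case against.** The strongest reply is that this is a slip of one letter group, not a choice of analysis. The model is called multilevel, the abstract promises mixed effects, practices are randomised, the sample size is inflated for clustering by practice, and the practice of each professional is recorded. With professionals as the unit of analysis, the practice is the obvious second level. That a COP random effect cannot be identified is itself evidence that nobody intended one. This stands: a slip is the likely explanation. A reader might infer from the sentence that the investigators have decided to ignore clustering by practice. The article does not support that; it follows only if the sentence is applied literally.

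The direction of the error is also not fixed. The step to a standard error that is too small assumes that the software sets the redundant variance to zero and the analyst accepts the result. A non-zero variance would make the standard error too large. This stands too, so the figures above describe one branch.

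Third, the inflation is modest: 6.4% at the planned ICC and about 6.0% among completers. The completer figure applies to the analysis without imputation. Under last observation carried forward, which the article also plans, the cluster size stays at five.

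It does not help to say that the analysis plan will settle the matter. The article is not silent on the random effect; it names one, and names the wrong one.

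**Conclusion.** Wrong as written. The sentence defining the random part of the primary model names the intervention where the design and the sample size call for the practice, and no other statement in the article corrects it. The error is more than clerical in effect, because it sits in the definition of the primary analysis and leaves the grouping factor open to later choice.

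The size is conditional. If the model collapses to ordinary regression, the standard error is about 5.5% too small and the type I error about 6.4%, at the article's own ICC of 0.03 and five per practice. The range of 5.5% to 9.8% rests on assumed ICCs of 0.01 to 0.10. The stronger claim, that the trial will certainly be analysed without regard to practice, is not established.

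**What to change.** In the analysis section, replace the statement that the model "also takes into account the random effect associated with the COP" by one saying that it includes a random intercept for the PCP, the unit of randomisation, with allocated arm as the fixed effect. The change should be recorded before the data are analysed.

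The cost is one sentence. Randomisation and data collection are untouched, the practice identifier is already among the recorded variables, and the sample size stays at 270 because the design effect of 1.12 is already in it.

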#### Professional and patient recruitment

We will hold face-to-face or virtual meetings with GPs and nurses from each selected PCP. Before PCP randomization, all included professionals (at least one per cluster) will complete both an informed consent form (Additional file 2) and the PPOS questionnaire, so as to minimize possible information bias. Also before PCP randomization, to avoid possible selection bias, the participating healthcare professionals will consecutively include patients. Patients who meet the inclusion criteria will complete, in their first visit, both an informed consent form (Additional file 3) and the PAM questionnaire.

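### The propensity score in the primary PPOS model addresses a selection problem that the design already removes; direct adjustment, with baseline PPOS and region added, would serve its purpose better

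*Protocol article*

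**What the plan says.** In the section on data collection, management and analyses, the primary model is a multilevel model for the change in PPOS, in which "the explanatory variable will be the dichotomous intervention variable (1 = COP/0 = control"). On adjustment it says "This model considers covariates such as age, sex and professional profile", and then: "We will use the propensity score to control for possible selection bias and enhance the accuracy of the model". The same section commits to intention-to-treat. It names neither baseline PPOS nor region as a covariate. It does not say what the score predicts, from which variables, or how the score enters the analysis.

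On the order of events, the abstract states "We will perform randomization after professionals and patients are selected". The recruitment section says of professionals: "Before PCP randomization, all included professionals (at least one per cluster) will complete both an informed consent form", together with the baseline PPOS. Of patients it says: "Also before PCP randomization, to avoid possible selection bias, the participating healthcare professionals will consecutively include patients". The Randomization section has an investigator who is blinded to practice identity and baseline scores, and who "will centrally perform randomization after professionals and patients are selected".

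The abstract describes the mixed model as serving "to estimate the effect of participating in the virtual community of practice".

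**The concern.** A propensity score is a tool for comparisons in which people reach their group by a process related to the outcome. Here the group is set by a random draw made after everyone is enrolled, and the article itself gives avoidance of selection bias as the reason for enrolling patients first. The stated purpose of the score therefore does not match the design.

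The stakes are modest. The step puts an analyst's choices (predictors, and use as covariate, weight or match) into the primary analysis without protecting against anything the planned covariates miss. It also stands where a more useful adjustment, for baseline PPOS and region, could be named.

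**Working it through.** **1. The plan's own figure.** Sample size section: difference 0.2, SD 0.5, alpha 0.05, power 80%, 100 per group. The two-sided formula gives 99 to 100. Design effect 1 + (5 − 1) × 0.03 = 1.12; 100 × 1.12 = 112; 112 × 1.2 = 134.4, rounded up to 135 per group, 270 in all. The figure reproduces, and nothing below changes it.

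**2. What the score could estimate.** 27 of 54 practices, nine of 18 in each region, go to each arm. Every professional's true probability of the virtual COP is 27/54 = 0.5, whatever their characteristics. A fitted score can pick up only chance imbalance or, among completers, imbalance due to loss. If it is fitted by logistic regression on the covariates already in the model, its logit is a linear combination of them and adds no information.

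**3. Does it add anything beside the covariates?** Simulation, 1,500 runs per setting. From the protocol: 54 practices balanced in three regions, ICC 0.03, SD 0.5, difference 0.2, and 5 × 0.8 = 4 completers per practice (108 per arm). Assumed: five covariates explaining 0, 10 or 25% of outcome variance; linear models with cluster-robust errors stand in for the mixed model. Without any score or covariate the estimate was unbiased under the null (means −0.0007 to 0.0003; type I error 4.9 to 5.2%). Simulated power:

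| Analysis | 0% | 10% | 25% |
|---|---|---|---|
| Covariates only | 78% | 83% | 89% |
| Covariates plus score | 79% | 83% | 89% |
| Score as sole covariate | 78% | 78% | 82% |
| Inverse weighting, no covariates | 78% | 78% | 79% |
| 1:1 caliper matching, no covariates | 72% | 69% | 72% |

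At 25% the empirical SD of the estimate was 0.0635 with covariates and 0.0636 with the score added. Score alone and weighting gave the same spread (0.0636). They show less power there because the standard error as computed does not credit the gain.

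**4. Differential loss.** Assumed scenario, no true effect, 1,000 runs: about 20% loss, related to a measured covariate in the COP arm only, with that covariate explaining 10% of the variance. Unadjusted bias was 0.027 PPOS points. Covariates alone, score alone and both together each gave −0.001.

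**5. Cost of the score.** A second simulation used the change score, assumed a baseline-to-follow-up correlation r = 0.5, and took seven score predictors unrelated to outcome. Power = Φ(0.2/SE − 1.96).

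- Change model: SE 0.0700, power 82%.
- Score added: SE 0.0711, power 80%.
- Weighting: SE 0.0714, power 80%.
- 1:1 matching, discarding 19.7%: SE 0.0762, power 75%.

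By formula, SE = 0.5 × √(2 × 1.12/108) = 0.0720, power 79.3%. Losing a further 20% leaves 86.4 per arm: SE 0.0805, power 70.0%.

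**6. What direct adjustment for baseline would bring.** With four completers per practice the design effect is 1 + 3 × 0.03 = 1.09, and √(2 × 0.25 × 1.09/108) = 0.0710. Multiply by √(2(1 − r)) for unadjusted change and by √(1 − r²) with baseline as covariate. The correlation is not in the article, so a range is shown; the ICC is taken as the same for both analyses.

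| r (assumed) | SE, change | SE, baseline-adjusted | Power |
|---|---|---|---|
| 0.3 | 0.084 | 0.068 | 66% → 84% |
| 0.5 | 0.071 | 0.062 | 80% → 90% |
| 0.7 | 0.055 | 0.051 | 95% → 98% |

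The second simulation, adjusting for baseline and region at r = 0.5, gave 0.0617 against 0.0700.

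**The case against.** The strongest defence is that the score has two stated purposes, and that the second, accuracy, is legitimate. The plan expects 20% loss and will report analyses without imputation, so completer comparisons will be made and measured imbalance between completers can arise. A score does correct that, as step 4 shows. This stands: it would be wrong to say that the score cannot reduce bias. But the planned covariates achieve the same, so it remains redundant.

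Three stronger readings are tempting, and the article does not support them.

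- **That the score will cost power or discard professionals.** This applies materially to matching or trimming, neither of which is mentioned. The stated aim of improving the model fits a covariate or a weight better, and there the change in standard error is about 0.001.
- **That the score breaks intention-to-treat by modelling who takes part in the COP.** The explanatory variable is coded COP versus control and intention-to-treat is promised, so allocation is the natural reading. Only the abstract's looser phrase points the other way. If participation were modelled, the comparison would no longer be the randomised one. At the 30% acceptance and 3% activity cited under strengths and limitations, 32 or 3 participants against 108 controls would give about 47% or 10% power.
- **That the score wrongly treats professionals as individually assigned.** The article does not say how it is fitted. Such detail may lie in the full protocol or the analysis plan, and its absence here is not a fault.

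The gain from baseline adjustment in step 6 is also not a measure of harm from the score. It shows what the accuracy aim could obtain by another route.

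**Conclusion.** The point holds in limited form. The selection-bias rationale does not fit a trial that enrols before it randomises, and no further detail on how the score is built would make it fit. Beside direct adjustment for the same variables the score adds nothing measurable. Kept as an extra covariate or weight it is close to harmless (standard error 0.070 versus 0.071), so this is an avoidable step rather than a threat to validity.

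The practical value lies in the replacement. Adding baseline PPOS and region lowers the standard error to about 0.062 if r = 0.5; the relative gain is larger at lower correlations and smaller at higher ones. The simulations rest on the protocol's SD, ICC, cluster size and loss, and on assumed covariate strength, loss mechanism and r.

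**What to change.** Remove the propensity score from the primary analysis. State that the mixed model for PPOS compares practices by allocated arm and adjusts for prespecified baseline PPOS, region (within which the practices are balanced), age, sex and professional profile. The response may stay as change: once baseline is a covariate, the arm effect is the same as for the final score.

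If a score is kept, state that it models allocation, uses baseline variables only and discards nobody.

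In the abstract, describe the estimate as the effect of allocation to the virtual COP, to agree with the intention-to-treat analysis, and label any participation-based analysis as supplementary.

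The cost is wording only, before the analysis starts. Baseline PPOS and region are already collected, and the sample size stays at 270.

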### Sample size

We calculated the required number of primary healthcare professionals for the purpose of comparing two independent means, considering as significant a post-intervention mean difference of 0.2 points and a common standard deviation of 0.5 points in the PPOS questionnaire between the e-MPODERA virtual COP intervention and control groups [29]. Each group will need 100 professionals, assuming alpha error of 0.05 and power of 80%. Since we will randomize by clusters, we have adjusted the sample size to take into account the design effect. Considering an intraclass correlation coefficient of 0.03 and assuming an average size per cluster of five healthcare professionals, we obtained a design effect of 1.12 [30]. Given these assumptions and expecting 20% loss to follow up after 12 months, we calculated a sample size of 270 healthcare professionals (135 professionals per group). The recruited healthcare professionals will, in turn, recruit a total of 1382 patients (assuming 20% loss to follow-up), the number that is required to detect a mean difference between the two groups of 4 points in the Patient Activation Measure questionnaire (PAM) scale [28].

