### Recruitment

Table 1 depicts the various stages of the e-MPODERA trial.

**Table 1 Tab1:** e-MPODERA randomized controlled trial stages

Stage	Procedure	
Stage 1 1^st^ month	Face-to-face or virtual meetings with the selected PCPs in each of the 3 Spanish regions. Invitation to participate. Participation agreement form signed by the PCP director	
Stage 2 1^st^ month	Face-to-face or virtual meetings in each selected PCP. Invitation to participate. Informed consent form signed by professionals who agree to participate	
Stage 3 2^nd^ month	PAM questionnaire administration to all eligible patients (baseline)	
Stage 4 2^nd^ month	PPOS questionnaire administration to all included professionals (baseline)	
Stage 5 2^nd^ month	PCP randomization	
Stage E 6 2-13^th^ month	Intervention group Virtual community of practice	Control group Usual training
Stage 7 14^th^ month	PPOS questionnaire administration to all included professionals (post intervention)	
Stage 8 14 − 15^th^ month	PAM questionnaire administration to all eligible patients (post intervention)	

*PCP* Primary-care practice, *PAM* Patient Activation Measure, *PPOS* Patient-Practitioner Orientation Scale

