### Outcome measures

#### Primary outcome

##### Healthcare professional attitudes

Specific measurement: the PPOS questionnaire (Additional file 4), developed by Krupat et al. in 1999 [27] will be used: this is a validated self-administered questionnaire containing 18 items scored on a 6-point Likert scale (1–6) that has been demonstrated to have very good psychometric properties [12, 27]. Professionals are classified by the PPOS into 3 categories according to their patient-centeredness score: low (≤4.57), medium (>4.57 and < 5), or high (≥5) [27]. We will translate and adapt the PPOS instrument for Spanish using the forward and back-translation procedure and will validate it within the e-MPODERA trial.

Specific metrics: change from baseline

Methods of aggregation: we will measure the mean of the PPOS questionnaire score. Time points: we will measure the primary outcome at the individual level by administering the PPOS questionnaire at baseline and at 12 months.

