#### Secondary outcome

##### Patient level of activation

Specific measurement: we will assess the patient level of activation with the PAM activation questionnaire (Additional file 5). The PAM activation questionnaire, which assesses activation in patients with chronic diseases, is the most widely used tool to measure patient engagement in self-care [31]. A short version of 13 items developed by Hibbard in 2005 [28] evaluates patient beliefs, knowledge and confidence in terms of a wide range of health-related behaviours. It uses a 4-point Likert-type scale (1–4) with a total score that is translated into a scale ranging from 0 to 100 (100 is the highest level of activation) to make interpretation easier. A version has been translated into Spanish and has been validated [32]. We will use the Insignia Health PAM® Survey (http://www.insigniahealth.com/products/pam-survey) in this project.

Specific metrics: we will assess change from baseline. Methods of aggregation: we will measure the mean of the PAM questionnaire score. Time points: we will measure the secondary outcome at the individual level by administering the PAM questionnaire at baseline and at 12 months.

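### PPOS and PAM are measured only twice, so last observation carried forward gives every dropout a change of exactly zero, and no version of the analysis is named as primary

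*Protocol article*

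**What the plan says.** All statements are in the protocol article.

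- **Measurement times.** Under Outcome measures, the primary outcome is obtained as follows: "we will measure the primary outcome at the individual level by administering the PPOS questionnaire at baseline and at 12 months". The secondary outcome is obtained in the same way, "by administering the PAM questionnaire at baseline and at 12 months". Table 1 (Recruitment) shows one later PPOS administration, in month 14, and no interim one.
- **Response variable.** Under Data collection, management and analyses, for the multilevel model of the PPOS, "the response variable will be the difference between initial and final scores in the questionnaire administered to participating professionals".
- **Population and missing data.** The same section commits to intention to treat ("We will perform intention-to-treat analyses using the statistical software") and then says: "We will use the last observation carried forward to impute missing data and will report analyses with and without imputation". It names no other imputation method and does not say which of the two versions decides the trial.
- **Expected loss.** The Sample size section allows for missing outcomes: "expecting 20% loss to follow up after 12 months".

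**The concern.** Carrying an observation forward needs an intermediate observation if it is to differ from the starting value. Here there is none. For a change-score outcome the rule therefore amounts to assuming that every professional and patient lost to follow-up stayed exactly where they began, and then analysing that assumption as if it were data.

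Two things are at stake. The estimated effect mixes real changes with zeros, so it can differ from the effect in everyone randomized. The imputed zeros also enter as observed values with no uncertainty of their own, so the standard error is too small for the information collected. Both affect the estimate and confidence interval for the primary outcome, and the same rule applies to the PAM.

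**Working it through.** **Inputs from the Sample size section.** Difference 0.2, SD 0.5, alpha 0.05, power 80%, intraclass correlation 0.03, five professionals per practice, 20% loss, 135 professionals per group.

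**The plan's own figure.** Per group, 2 × (1.96 + 0.8416)² × 0.5² / 0.2² = 98.1, or 99 after rounding up; the plan states 100. The design effect is 1 + (5 − 1) × 0.03 = 1.12. Then 100 × 1.12 = 112, and 112 × 1.2 = 134.4, giving 135 per group and 270 in total. The stated size is reproduced when loss is added as a 20% surcharge.

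**Inputs that are assumed because the protocol gives none.** These are the SD of the change score, the mean change in controls, and the loss in each arm. With SD 0.5 at each time point, the change SD is s = 0.5 × √(2(1 − ρ)), which equals 0.5 when the correlation ρ between baseline and 12 months is 0.5. Dropouts are assumed to change like completers unless stated.

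**Step 1, number of zeros.** 0.20 × 270 = 54 professionals, and 0.20 × 1382 ≈ 276 patients. This needs no assumption beyond the planned loss.

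**Step 2, estimate.** In an arm with loss d and true mean change μ, the imputed mean is (1 − d)μ. The bias in the difference is −(d_COP × μ_COP − d_control × μ_control). With 20% loss in both arms and a true effect of 0.20, the estimate is 0.8 × 0.20 = 0.16, whatever the common time change.

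**Step 3, standard error.** The imputed change has variance (1 − d)(s² + μ²) − ((1 − d)μ)². With s = 0.5, control change 0 and COP change 0.20:

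- COP arm: 0.8 × (0.25 + 0.04) − 0.16² = 0.2064
- Control arm: 0.8 × 0.25 = 0.2000
- SE with carry-forward: √(0.4064 × 1.12 / 135) = 0.058
- SE with no missing data: √(0.50 × 1.12 / 135) = 0.064
- SE with completers only (108 per arm, same design effect): √(0.50 × 1.12 / 108) = 0.072

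**Step 4, power and coverage at equal loss.** Carry-forward: 0.16 / 0.0581 = 2.75, power about 79%. Completers: 0.20 / 0.0720 = 2.78, power about 79%. The estimate and its standard error shrink together. A 95% interval from the carry-forward analysis covers 0.20 about 89% of the time.

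**Step 5, range over ρ.** The estimate of 0.16 does not depend on ρ.

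| ρ | SE, carry-forward | SE, no missing data | SE, completers |
|---|---|---|---|
| 0.3 | 0.069 | 0.076 | 0.085 |
| 0.5 | 0.058 | 0.064 | 0.072 |
| 0.7 | 0.045 | 0.050 | 0.056 |

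**Step 6, unequal loss (scenarios, s = 0.5).**

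| Loss COP / control | True effect | Control change | Carry-forward estimate | Consequence |
|---|---|---|---|---|
| 30% / 10% | 0.20 | 0 | 0.7 × 0.2 − 0 = 0.14 | power 67% (completers 79%) |
| 30% / 10% | 0.20 | 0.2 | 0.7 × 0.4 − 0.9 × 0.2 = 0.10 | power 38% (completers 79%) |
| 10% / 30% | 0.20 | 0.2 | 0.9 × 0.4 − 0.7 × 0.2 = 0.22 | bias away from zero |
| 20% / 20% | 0 | 0.1 | 0 | type I error 5% |
| 30% / 10% | 0 | 0.1 | 0.07 − 0.09 = −0.02 | type I error about 6% |
| 30% / 10% | 0 | 0.2 | 0.14 − 0.18 = −0.04 | type I error about 10–11% |

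A cluster simulation of the last row (27 practices of five per arm, intraclass correlation 0.03, t test on practice means, 8000 runs) gave 10.4%.

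**The case against.** The strongest reply is that the sentence stating the imputation also promises results without it. That analysis contains no imputed zeros, and when loss is unrelated to outcome it is unbiased, so a reader would see both. This stands as mitigation. It does not settle the matter, because the article gives no rule for which result counts if the two differ. A statistical analysis plan that is not shown might name the primary version, but the imputation rule itself is already stated here and fits a two-time-point design badly. Nor is the non-imputed change-score model a complete answer: baseline score is not among the covariates given as examples, so it is not protected if loss depends on the baseline score.

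A second reply is that zero change may be realistic for some dropouts. The Study strengths and limitations section cites similar experiences in which only 3% of professionals became active. If those lost truly do not change, carry-forward is unbiased. The protocol does not argue this, however, and does not support it for controls who receive usual training.

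A reader might infer that the rule always biases the result, costs power or inflates the type I error. The documents do not support that. With equal loss and no effect, bias is zero and type I error is 5%; with equal loss and a true effect, power is practically unchanged. The 10–11% error rate needs both 30% against 10% loss and a drift of 0.2 in both arms, which is as large as the whole target effect. The protocol gives a single 20% loss and no drift. Differential loss is plausible among professionals, who cannot be masked and take part in the COP voluntarily. The argument is weaker for the PAM, since the Masking section says patients are blind to allocation.

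**Conclusion.** The point holds in a conditional form. It is certain from the text that carry-forward means zero change for everyone without a 12-month score, about 54 of 270 professionals at the planned loss. If dropouts would have changed like completers and loss is equal, the target difference of 0.20 becomes about 0.16, a 20% attenuation. With a change SD of 0.5, the standard error is then about 10% below that of fully observed data (0.058 against 0.064). Power is about 79% with or without the imputation in that setting.

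Unequal loss combined with a time trend can bias the estimate in either direction, so the method cannot be defended as reliably conservative. The sizes given for those cases are scenarios, not predictions. Because a non-imputed analysis is also promised, this is a weakness that should be corrected before analysis, not one that invalidates the trial.

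**What to change.** Drop last observation carried forward as the imputation for the intention-to-treat analysis. Name one primary analysis that is valid under missing-at-random, conditions on baseline score and respects clustering by practice. Either of these would do:

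- a likelihood-based mixed model on all observed PPOS scores, with baseline and 12 months as outcomes and random effects for practice and professional; or
- multilevel multiple imputation that includes baseline score, arm, region and professional profile, all of which are known or already collected.

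With a single follow-up, the mixed model gains little over a baseline-adjusted analysis of completers. Its main value here is that it conditions on baseline and is declared in advance. Add a delta-adjusted sensitivity analysis in which the assumed outcome of dropouts is shifted, separately by arm, and do the same for the PAM.

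The cost is revised analysis wording and modest programming; no new data are needed. The downside is that the primary result then rests on missing-at-random, which the sensitivity analysis is there to examine.
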